## Abstract

**Background:**

Sarcopenia is defined by a loss of muscle strength associated to a decrease in skeletal muscle mass. Ageing greatly contributes to sarcopenia as may many other factors such as cancer or androgen deprivation therapies (ADT). This cohort study aims to evaluate (1) the prevalence of muscle disorders and sarcopenia in older patients before initiation of intermediate to high risk prostate cancer treatment with ADT and radiotherapy, and (2) the occurrence and/or aggravation of muscle disorders and sarcopenia at the end of cancer treatment.

**Methods:**

This cohort study is monocentric and prospective. The primary objectives are to determine the risk factor of sarcopenia prevalence and to study the relationship between ADT and sarcopenia incidence, in patients 70 years and older with histologically proven localized or locally advanced prostate cancer, addressed to a geriatrician (G8 score ≤14) for comprehensive geriatric assessment (CGA) in Marseille University Hospital. Secondary objectives encompass, measurement of sarcopenia clinical criteria along prostate oncological treatment; evaluation of the quality of life of patients with sarcopenia; evaluation of the impact of socio-behavioral and anthropological factors on sarcopenia evolution and incidence; finally the evaluation of the impact of ADT exposure on sarcopenia. Sarcopenia prevalence was estimated to be between 20 and 30%, therefore the study will enroll 200 patients.

**Discussion:**

The current guidelines for older patients with prostate cancer recommend a pelvic radiotherapy treatment associated to variable duration (6 to 36 months) of ADT. However ADT impacts muscle mass and could exacerbate the risks of sarcopenia. Our study intends to assess the specific effect of ADT on sarcopenia incidence and/or worsening as well as to estimate sarcopenia prevalence in this population. The results of this cohort trial will lead to a better understanding of sarcopenia prevalence and incidence necessary to further elaborate a prevention plan.

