## Methods / Design

### Design

This monocentric cohort study will assess the prevalence of sarcopenia in 200 men with localized or locally advanced prostate cancer treated by radiotherapy associated with androgen deprivation therapy. The protocol was designed in respect of the recommendations of the Standard Protocol Items: Recommendations for Interventional Trials (SPIRIT) statement.

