### Participants

All consecutive patients with intermediate or high risk prostate cancer addressed for CGA, who fit the inclusion/exclusion criteria and consent to participation to the trial, will be enrolled. The details of the inclusion and exclusion criteria are provided in Fig. 1. The main inclusion criteria are patients over 70 years old with histological diagnosis of localized or locally advanced prostate cancer according to D’Amico classification [14] with treatment decision set on radiotherapy associated to ADT; requiring a CGA based on the SIOG recommendations (G8 score ≤14 )[15].

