#### Treatment Phase

Patient will benefit from standard cancer treatment for localized and locally advanced prostate cancer, i.e.: radiotherapy associated to ADT 6 to 36 months [4, 5]. Treatment phase will be handled by urologist and radiotherapist.

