### Endpoints/Evaluation criteria

#### Primary endpoint

The primary endpoint is:The evaluation of sarcopenia prevalence for patients 70 years and older with localized or locally advanced prostate cancer before treatment initiation.

The geriatrician will screen for suspicion of sarcopenia using the SARC-F questionnaire and muscle strength assessment as recommended by the EWGSOP2 guidelines [10]. Patient whose SARC-F score is superior or equal to four out of ten are at risk of sarcopenia and will undergo muscle strength assessment. Patient with impaired muscle strength (either handgrip strength under 27 kg for men and 16kg for women or five chair stand in more than 15 seconds) are considered with probable sarcopenia [10]. To ascertain sarcopenia diagnosis, SMI will be estimated using the Appendicular Skeletal Muscle Mass (ASMM) measured with dual-energy X-ray absorptiometry (DXA) [17], adjusted for body size (ASMM/height^2^). Chosen cut-off point for low SMI indicating sarcopenia diagnosis as per EWGSOP2 guidelines is <7.0 kg/m2 [10]. Sarcopenia severity will be evaluated using Timed up and Go test and Gait speed assessment.

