#### Secondary endpoints

The secondary endpoints are:The evaluation of sarcopenia incidence in patients 70 years and older with localized or locally advanced prostate cancer a year after the end of ADT. Sarcopenia assessment will be lead at enrollment and a year after ADT end.Evaluate the evolution of the physical performances by the measurement of mobility (Timed Up and Go test, gait speed and chair stand test) at enrollment and after ADT in patients 70 years and older with localized or locally advanced prostate.Evaluate quality of life (QoL) evolution before and after ADT for patient 70 years and older with localized or locally advanced prostate with or without sarcopenia. QoL will be evaluated using EORTC QLQ-c30 questionnaires and ELD-14 module at enrollment and a year after ADT end.Evaluate impact of socio-behavioral, anthropological and geriatric factors on sarcopenia prevalence for patients 70 years and older with localized or locally advanced prostate and on its incidence after ADT. Geriatric factors such as Autonomy (score <6 on Activity of Daily Living (ADL) Scale and score <4 on Instrumental Activity of Daily Living (IADL) scale) [18], nutrition (Weight, Body Mass index (BMI), Albumin, Mini Nutritional Assessment (MNA) )[19]., cognitive status (Mini Mental State Examination (MMSE)) [16], mood (Geriatric Depression Scale (GDS)) [20], polypharmacy, and comorbidities will be assessed by CGA. Demographic information such as age, gender, presence of a caregiver, urban or countryside way of living and physical activity (number of days when patient exercise an hour at least).Evaluate impact of ADT of patients 70 years and older with localized or locally advanced prostate on sarcopenia. Oncological data such as cancer stage and anatomy; testosterone and PSA levels at enrollment and a year after ADT end; treatment protocol for radiotherapy and ADT will also be collected.

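### The article promises the specific effect of ADT on sarcopenia, but every patient receives ADT plus radiotherapy, so the before-after change cannot be attributed to ADT

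*Protocol article*

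**What the plan says.** Three places in the protocol article set an aim about ADT itself. The abstract's Discussion states "Our study intends to assess the specific effect of ADT on sarcopenia incidence and/or worsening". The abstract's Methods lists, among the primary objectives, "to study the relationship between ADT and sarcopenia incidence", and names the impact of ADT exposure as a secondary objective. The Secondary endpoints section includes "Evaluate impact of ADT of patients 70 years and older with localized or locally advanced prostate on sarcopenia".

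The design is a single treated cohort. The Design section describes "200 men with localized or locally advanced prostate cancer treated by radiotherapy associated with androgen deprivation therapy". The Participants section admits patients "with treatment decision set on radiotherapy associated to ADT". The Treatment Phase section gives the standard treatment as "radiotherapy associated to ADT 6 to 36 months".

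On timing, baseline prevalence is measured in patients "with localized or locally advanced prostate cancer before treatment initiation" (Primary endpoint), and the incidence endpoint says "Sarcopenia assessment will be lead at enrollment and a year after ADT end" (Secondary endpoints). Follow-up – T1 also dates T1 from completion of standard treatment. It gives a total study duration of 48 months with 24 months of recruitment.

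The Data analysis section takes T0 as the baseline for incidence and compares it with T1. It refers to two groups without defining them. The only split described elsewhere is with or without sarcopenia, under the quality-of-life endpoint.

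The main Discussion states a different, descriptive aim: prevalence, and incidence following ADT combined with radiotherapy.

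**The concern.** A specific effect of ADT means the difference between what happens with ADT and what would have happened without it. A cohort in which every patient is planned for ADT plus radiotherapy holds no information on the second quantity. The article itself names ageing and cancer as causes of sarcopenia (abstract Background; Background), and these patients are men of 70 or over with an impaired G8 screen. New cases between T0 and T1 are therefore to be expected even if ADT did nothing.

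The only exposure contrast inside the cohort is how much ADT a patient received. The visit schedule ties its duration to the length of observation, so that contrast does not isolate ADT either.

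What is at stake is the conclusion the study may draw. The main Discussion says the results may lead to prevention programmes being added to ADT. A before-after rise reported as an ADT effect would overstate the evidence for that step.

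**Working it through.** **1. The plan's own figure.** The section on sample size gives a 95% confidence interval width of 0.115 to 0.131 for N = 200 and a prevalence of 20% to 30%. The exact (Clopper-Pearson) interval reproduces it:
- 40/200: 0.1469 to 0.2622, width 0.1153.
- 60/200: 0.2374 to 0.3686, width 0.1313.

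The figure is sound, but it concerns baseline prevalence only. No figure in the article supports an ADT effect.

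**2. Aim against design.**
- Aim: specific effect, impact or relationship of ADT (abstract Discussion, abstract Methods, Secondary endpoints).
- Exposure: radiotherapy plus ADT for all (Design, Participants, Treatment Phase).
- Comparison: T0 against T1 (Data analysis).

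The observed change is thus the sum of ADT, radiotherapy, cancer, ageing over the interval and any recovery during the year off ADT. One before-after difference cannot separate five components.

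**3. Interval length.** Inputs are ADT duration D of 6 to 36 months (Treatment Phase) and T1 at ADT end + 12 months (Secondary endpoints).

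Interval ≈ D + 12 months, apart from the lag between T0 and ADT start and visit scheduling.
- D = 6: 18 months.
- D = 36: 48 months.
- Ratio: 48/18 = 2.67.

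If T0 coincides with ADT start and T1 is on schedule, duration and elapsed time differ by a constant and their correlation is 1.

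**4. How much of that range is reachable.** A patient enrolled at month m reaches T1 within 48 months only if m + D + 12 ≤ 48, so D ≤ 36 − m.
- m = 0: D up to 36 months.
- m = 24: D up to 12 months.

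The 48-month interval is available only to a patient enrolled at the very start.

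**5. Illustration with no ADT effect.** The article gives no background incidence, so the hazard h is an assumption, constant over time. Risk = 1 − exp(−h × months/12).

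| h per year (assumed) | 18 months | 48 months | Ratio |
|---|---|---|---|
| 5% | 7.2% | 18.1% | 2.5 |
| 8% | 11.3% | 27.4% | 2.4 |
| 10% | 13.9% | 33.0% | 2.4 |

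The ratio hardly depends on the assumed hazard; it comes from the interval lengths. It compares the two extremes of step 3 and is a worst case.

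**6. Whether modelling interval length would rescue a duration analysis.** With log(interval) as an offset, the duration coefficient is free of elapsed time only if the hazard is constant. Suppose instead a Weibull hazard with shape 1.5 (assumption) and no ADT effect. The cumulative hazard then grows by 2.67^1.5 = 4.35, while the offset allows for 2.67. The model would report a rate ratio of 4.35/2.67 = 1.63 for 36 against 6 months. Adjusting for age at baseline does not remove this.

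**The case against.** The strongest reply is that the Data analysis section plans no comparison by ADT duration. Its chi-square, Fisher and t tests compare all patients between the two assessments. Its two groups are not said to be short against long ADT, and the Secondary endpoints section says only that treatment data will be collected. This stands. A reader might infer that a spurious dose-response is built into the planned incidence analysis; the article does not support that, because it specifies no such analysis.

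A second reply is that the regression covariates are not listed and that ADT dates are collected, so interval length may be handled in a fuller document. This also stands. The article's silence on a term for elapsed time is not counted as an error here.

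A third is that the descriptive aim is already present. The abstract's Background, the Background section and the main Discussion all speak of occurrence or incidence after treatment, and the words about a specific effect appear once. This is true, but it does not dispose of the point: the abstract's Methods and the Secondary endpoints section also direct the study towards an ADT relationship or impact. A comparator cannot be left to an analysis plan when eligibility requires a decision for radiotherapy plus ADT.

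**Conclusion.** The stated aim exceeds what the design can deliver. Without an ADT-free group, the T0-T1 change describes what follows radiotherapy plus ADT and cannot be credited to ADT alone. This rests on the article's own text and needs no numerical assumption.

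The ratio of about 2.4 has a narrower standing. It assumes a constant 8% per year hazard and compares 18 with 48 months, the latter rarely reachable within the study. It shows what a duration analysis could produce with no ADT effect; it is not the bias of any analysis the article specifies.

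The primary endpoint, prevalence before treatment, and the sample size based on it are unaffected. The point should be acted on because it changes what the study may conclude.

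**What to change.** - Align the abstract's Methods, the abstract's Discussion and the Secondary endpoints section with the main Discussion. State the aim as sarcopenia incidence and change from before treatment to one year after radiotherapy plus ADT, with no attribution to ADT alone.
- Report incidence together with the T0-T1 interval, for example per person-year, noting that follow-up status is assessed only once, at T1. The time of onset is then unknown, and recovery before T1 would go unseen.
- Label any association with ADT duration exploratory, and state that it cannot be separated from elapsed time without assuming the shape of the hazard. A model with an offset for interval length should not be presented as removing this confounding.

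The cost is wording and one reporting convention, using dates already collected. No added patients or visits are needed. The downside is a more modest causal claim.

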**Trial registration:**

The protocol was registered to the French drug and device regulation agency under the number 2019-A02319-48, before beginning the study (11/12/2019). The ClinicalTrials.gov identifier is NCT04484246, registration on the ClinicalTrials.gov (https://clinicaltrials.gov/ct2/show/NCT04484246).

## Background

Prostate cancer is the most common cancer for men over 60 years old worldwide according to 2020 Globocan’s data [1, 2]. For intermediate or high risks forms of prostate cancer, radiotherapy associated to androgen deprivation therapy (ADT) for 6 to 36 months is the reference treatment [3–5]. ADT induces several side effects including, anemia, alteration of physical functions, decrease of quality of life and activity [6]; in parallel, androgen inhibitors are known to be associated with metabolic effects that could result in obesity, diabetes, cardiovascular afflictions, sarcopenia or osteoporosis [7–9].

Sarcopenia is a degenerative muscle disorder characterized by loss of muscle strength and skeletal muscle mass, with or without an increase of fat mass (sarcopenic obesity) [9]. Aging, but also poor nutrition, inactivity or cancer can contribute to sarcopenia. Moreover, sarcopenia is a risk factor of early death, falls and loss of independence or/and mobility in older populations [9].

Sarcopenia screening and diagnosis are based on a combination of measures of muscle mass and muscle strength that vary according to the international guidelines and consensus [10–12]. Measures of physical performance are used to appreciate the severity of the disease.

Sarcopenia incidence in older patients is poorly known but awareness is growing among clinicians, as the criteria to diagnose malnutrition for patients 70 years and older, edited by the French High Health Authority (HAS) [13], just recently were amended to include sarcopenia. The diagnosis is based on the new updated recommendations of the revised European guidelines (EWGSOP2) [10]. Sarcopenia screening in not yet part of the guidelines on older patients’ cancer management. In this particular context, our study aims to document (1) the prevalence of muscle disorders and sarcopenia in old patients before initiation of prostate cancer treatment with ADT and radiotherapy, and (2) the occurrence and/or aggravation of muscle disorders and sarcopenia at the end of cancer treatment.

## Methods / Design

### Design

This monocentric cohort study will assess the prevalence of sarcopenia in 200 men with localized or locally advanced prostate cancer treated by radiotherapy associated with androgen deprivation therapy. The protocol was designed in respect of the recommendations of the Standard Protocol Items: Recommendations for Interventional Trials (SPIRIT) statement.

### Setting

Patients will be screened in the Radiotherapy Department, the Urology Department, the Urologic Surgery and Transplantation Department and finally in the Internal Medicine, Geriatrics and Therapeutic Department of Marseille University Hospital (AP-HM). Epidemiology and Health Economics Unit, will take part in the methodology and will perform the data analysis.

The protocol version 2 of the 21^st^ October 2019 was accepted by the committee of persons’ protection “Ile de France IV” on the 24/10/2019, first patient was enrolled on the 11/12/ 2019.

### Participants

All consecutive patients with intermediate or high risk prostate cancer addressed for CGA, who fit the inclusion/exclusion criteria and consent to participation to the trial, will be enrolled. The details of the inclusion and exclusion criteria are provided in Fig. 1. The main inclusion criteria are patients over 70 years old with histological diagnosis of localized or locally advanced prostate cancer according to D’Amico classification [14] with treatment decision set on radiotherapy associated to ADT; requiring a CGA based on the SIOG recommendations (G8 score ≤14 )[15].

**Fig. 1 Fig1:**
[figure not shown]
HoSAGE Study Flow Chart

The main exclusion criteria are patients under 70 years old, patients with metastatic prostate cancer showing a Mini-Mental State Examination (MMSE) score [16] under 10 out of 30.

### Recruitment and follow-up

#### Screening and enrollment - T0

Eligible patients will be identified by the radiotherapist and/or the urologist and/or the geriatrician. Patient over 70 years old screened with a G8 score ≤ 14/17 will be addressed to the geriatrician and benefit from full CGA and sarcopenia assessment: sarcopenia risk will be evaluated using the SARC-F questionnaire (Strength, Assistance walking, Rise from a chair, Climb stairs, and Falls questionnaire). Muscle strength will be assessed for patient at risk of sarcopenia (impaired SARC-F). For patient with probable sarcopenia (impaired muscle strength), sarcopenia diagnosis will be confirmed by measuring the skeletal muscle index (SMI). The severity of sarcopenia will also be evaluated.

#### Treatment Phase

Patient will benefit from standard cancer treatment for localized and locally advanced prostate cancer, i.e.: radiotherapy associated to ADT 6 to 36 months [4, 5]. Treatment phase will be handled by urologist and radiotherapist.

#### Follow-up – T1

A year after standard treatment completion, patient will once again benefit from CGA and sarcopenia assessment as described for T0.

Total duration of study will be 48 months, recruitment period will be 24 months and patient follow-up period, 12 months. A year after ADT end, patient will be contacted either by the geriatrician or the study coordinator to schedule the follow-up (T1). The study procedure and data collection are detailed in Table 1.

**Table 1 Tab1:** HoSAGE Study schedule of activities and procedures

	T0	Treatment phase	T1
Oncologist consultation	X	X	
Diagnosis	X		
G8 score ≤14	X		
Geriatrician consultation	X		X
Enlighten consent	X		X
Enrollment	X		X
CGA	X		X
Demographic information	X		X
Social isolation	X		X
Cognitive status (MMSE and clock drawing test)	X		X
Mood status (GDS)	X		X
Autonomy (ADL and IADL Score)	X		X
Nutritional status (BMI, MNA score and Albumin)	X		X
Mobility (OLGT, Gait speed)	X		X
Sarcopenia screening (SARC-F, Handgrip test and chair stand test)	X		X
If Sarcopenia risk suspected (SARC-F≥4/10), and Muscle strength is impaired, SMI will be measured by (DXA)^a^	X^a^		X^a^
Radiotherapy treatment (dates, dose delivered and number of fractions)		X	
Androgen deprivation therapy (dates, dose delivered, frequency, adverse events)		X	

^a^DXA assessment performed only if SARC-F score is ≥4/10 and muscle strength is impaired (either handgrip strength under 27 kg for men and 16kg for women or five chair stand test is performed in more than 15 seconds)

*CGA: Comprehensive Geriatric Assessment; MMSE: Mini Mental State Examination; GDS: Geriatric Depression Scale; ADL: Activity of Daily Living; IADL: Instrumental Activity of Daily Living; BMI: Body Mass Index; MNA: Mini Nutritional Assessment; OLGT: One Leg Balance Test; SARC-F: Strength, Assistance walking, Rise from a chair, Climb stairs, and Falls; SMI: Skeletal Muscle Index (appendicular muscular mass/seize*^*2*^*); DXA: Dual-energy X-ray*

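### A 48-month study with 24 months of recruitment cannot contain T1 for every patient: with ADT of 6 to 36 months the last T1 falls at month 72 or later

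*Protocol article*

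**What the plan says.** The calendar is in the protocol article under Follow-up – T1: "Total duration of study will be 48 months, recruitment period will be 24 months and patient follow-up period, 12 months". The same section places the second assessment after treatment: "A year after standard treatment completion, patient will once again benefit from CGA and sarcopenia assessment as described for T0". It then says that patients are contacted one year after ADT ends to arrange that visit. Secondary endpoints uses the same anchor: "Sarcopenia assessment will be lead at enrollment and a year after ADT end".

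Treatment Phase describes the treatment as "radiotherapy associated to ADT 6 to 36 months". The Abstract (Discussion) and Background give the same 6 to 36 months. The Primary endpoint section puts the baseline in patients with "localized or locally advanced prostate cancer before treatment initiation", so the ADT clock starts at or after T0.

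Participants says that all consecutive eligible, consenting patients are enrolled. The article sets no limit on enrolment by planned ADT duration, gives no earlier T1 for long courses, and makes no provision for T1 visits after month 48.

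**The concern.** The stated total duration, recruitment period, ADT range and T1 timing do not fit together. This is a conflict between figures that the article itself gives, not a detail left to a fuller document.

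The endpoints that need T1 are at stake: sarcopenia incidence, change in physical performance, change in quality of life, and the impact of ADT. For physical performance the text says only that it is measured after ADT, but Table 1 offers no post-treatment visit other than T1. These are listed as secondary endpoints, yet the Abstract names the relationship between ADT and sarcopenia incidence among the primary objectives.

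If month 48 is enforced as the end of data collection, whether a patient has a T1 depends on how long he received ADT and when he enrolled. That is not ordinary drop-out, because missingness is tied to the exposure under study. At the longest durations almost nobody would be observed, so adjustment would have to extrapolate.

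**Working it through.** **Inputs.** Total duration 48 months, recruitment 24 months, and 12 months from ADT end to T1 (Follow-up – T1). ADT duration D of 6 to 36 months (Treatment Phase). T0 before treatment (Primary endpoint). N = 200 (Sample size, power, and statistical methods).

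**Can the stated 48 months be reproduced?** Only in two ways:
- 24 + 12 + 12 = 48, which requires ADT of at most 12 months starting at T0.
- 36 + 12 = 48, which holds for a 36-month patient enrolled on day 1 and ignores recruitment.

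Neither covers the stated ADT range over the stated recruitment period.

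**Time from T0 to T1.** D + 12, so 6 + 12 = 18 months up to 36 + 12 = 48 months, if ADT starts at T0.

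**Last T1.** 24 + D + 12. A patient enrolled at month t reaches T1 by month 48 only if t ≤ 48 − 12 − D = 36 − D.

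**Share reaching T1 by month 48.** Assumptions: uniform accrual over 24 months and collection stopping at month 48. With lag g from T0 to ADT start, the share is min(1, max(0, (36 − D − g)/24)).

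| ADT (months) | Last T1, no lag | Share, no lag | Share, assumed 3-month lag |
|---|---|---|---|
| 6 | 42 | 100% | 100% |
| 12 | 48 | 100% | 87.5% |
| 18 | 54 | 75% | 62.5% |
| 24 | 60 | 50% | 37.5% |
| 30 | 66 | 25% | 12.5% |
| 36 | 72 | 0% (day-1 enrolment only) | 0% |

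**Total number with a T1.** The mix of ADT durations is not stated, so this can only be illustrated (no lag, before deaths or drop-out):
- Half 6 and half 18 months: 200 × (0.5 × 1 + 0.5 × 0.75) = 175.
- Half 6 and half 24 months: 200 × (0.5 × 1 + 0.5 × 0.50) = 150.
- Half 6 and half 36 months: 200 × (0.5 × 1 + 0.5 × 0) = 100.
- A quarter 6 and three quarters 36 months: 200 × (0.25 × 1 + 0.75 × 0) = 50.

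**Shift in exposure.** Suppose D were uniform over 6 to 36 months. The share with D ≤ 12 is 6/30 = 0.2, all observed. The remaining 24/30 = 0.8 are observed at an average of 50%. The total is 0.2 + 0.4 = 0.6, or 120 of 200. Mean ADT would be 21.0 months among those enrolled and 16.3 among those with a T1.

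**Primary endpoint.** The exact (Clopper-Pearson) 95% interval at N = 200 has width 0.1153 at 20% prevalence and 0.1313 at 30%. This reproduces the stated 0.115 to 0.131. That calculation uses T0 only.

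**The case against.** The strongest reply is that the article states a planned duration, not a data-closure rule. Patients are to be contacted a year after ADT ends, with no cut-off, so the sponsor may simply collect late T1 visits. This stands as a limit on the consequence: the selective loss is conditional on stopping at month 48. It does not remove the conflict, since 72 months are needed and 48 are stated.

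Four stronger readings are tempting, and the documents do not support them:
- A reader might infer that long-course patients drop out of every T1 endpoint altogether. The loss is graded: three quarters of 18-month and half of 24-month patients would still reach T1, and only courses close to 36 months are almost wholly lost.
- A reader might take "patient follow-up period, 12 months" as a misstatement of the interval from enrolment to T1. It reads naturally as the year from ADT end to T1, which the section states elsewhere. On that reading the 12 months is right, and the conflict lies between total duration, recruitment and ADT range.
- A reader might assume that the missing long exposures are those with the most muscle loss. The article says that ADT affects muscle but gives no relation with duration. The selection problem does not need that assumption.
- A reader might think the main result is compromised. The primary endpoint is prevalence at T0, and Data analysis requires only a T0 evaluation for it.

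**Conclusion.** The point holds as a calendar contradiction. On the article's own figures, the study needs at least 72 months to contain every T1, 24 more than stated, plus any lag between T0 and ADT start. This part rests on no assumption beyond the stated durations.

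The bias is conditional. If T1 collection ends at month 48, T1-based results would over-represent short courses and early enrolees. The shares by duration rest on uniform accrual and ADT starting at T0; a lag lowers them for courses near or above 12 months. The overall T1 sample cannot be fixed because the ADT mix is not given; the simple mixes above span 50 to 175 of 200. An incidence result would then be read as covering 6 to 36 months of ADT while the longest courses were barely observed.

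T0 prevalence and its interval width are untouched. The point concerns the study calendar, not which ADT duration is appropriate.

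**What to change.** Reconcile Treatment Phase, Follow-up – T1 and Secondary endpoints:
- Restate the total duration as at least 72 months plus any lag to ADT start.
- State that the 12 months runs from ADT end to T1, which is 18 to 48 months from enrolment if ADT starts at T0.
- Keep the already planned T1 visits open until the last patient reaches T1.
- Report T0 prevalence on the original schedule.

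The cost is a later final T1 report and a longer open period, with the coordination that this needs. No procedure is added. Trial status gives the study as still recruiting at submission, so the change was available then.

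If closure at month 48 is fixed, keep all observed T1 data, report T1 completeness by ADT duration, restate the expected T1 sample size, and limit the incidence and ADT-impact conclusions to the durations actually observed. Restricting the T1 analysis to courses of 12 months or less is not a good substitute. It would discard observed data from longer courses, and with any lag to ADT start the late-enrolled 12-month patients would still miss month 48 (87.5% reach T1 with an assumed 3-month lag).
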